### Outcome assessment

Data from patients were collected at baseline by reviewing medical records for clinical data and self-completed questionnaires for demographic data, including age, education level, ethnicity, duration of diabetes, and history of co-morbidities. Clinical data will be collected again at six and 12 months in similar fashions.

The ICDMS aimed to enable patients to achieve optimal glycaemic control and therefore, the primary outcome is HbA1c at 12 months. The proportion of patients with HbA1c ≤ 7% (ie. within the NHMRC guidelines for glycaemic control[15]; between 7.1% and ≤ 8%; between 8.1% and 10%; and greater than 10% will be calculated and compared between groups.

Secondary outcome measures include improvements in modifiable cardiovascular disease risk factors, and improvements in patient quality of life and diabetes self-efficacy. Improvements in modifiable cardiovascular disease risk factors include decreased total and low density lipoprotein (LDL) cholesterol and blood pressure (BP), increased levels of physical activity, and increased proportion of non-smoking participants. Additionally, the proportion of participants with BP and LDL cholesterol at target will be assessed at 12 months. Quality of care indicators included the proportion of patients with microalbuminuria on Angiotensin-Converting Enzyme (ACE) inhibitors or Angiotensin 2 Receptor Antagonists (A2RB); the proportion of patients with dyslipideamia on statins or fibrates (if indicated and tolerated); and the proportion of patients on prophylactic aspirin (as was accepted best practice at the commencement of this study).

Changes in health status will be assessed using the EuroQoL 5-Dimension (EQ-5D) scale. This standardised, five item descriptive system and visual analog scale measures mobility, self-care, pain, usual activities and anxiety and contributes to a 'utility' score[16] and was chosen to enable an international comparison of the cost-effectiveness of the project. Changes in diabetes self efficacy, or an "individual's judgement of confidence to carry out tasks specific to diabetes management" will be assessed using the 18-item Diabetes Self Efficacy Scale. This scale assesses an individual's sense of certainty or uncertainty about their ability to manage their condition, and their perceived ability to follow diabetic routines, self-treat, exercise and follow an appropriate dietary plan[17]. Changes in the prevalence and severity of depression will be assessed in the intervention group using the depression module of Patient Health Questionnaire (PHQ-9)[18] but not in the control group as it was beyond the scope of this project to provide clinical care for any control patients identified with significant levels of depression via this assessment.

### Statistical analysis

Baseline characteristics that differ significantly between the two patient groups and the two groups of general practices will be identified using descriptive statistics and adjusted for in all multivariate analyses. Characteristics of participants who complete and withdraw will be compared. To ensure the generalisability of the results, the number of non-participants, their age and gender, and their reason for non-participation will be recorded.

Analyses of primary outcomes will be done on an intention to treat basis assuming return to baseline values for any patients who do not complete follow-up. Measures of the outcome value at baseline will be included in the regression analysis as a covariable. Other covariables may include any characteristics that are not balanced between the groups at baseline. A sensitivity analysis will investigate the effect of participant loss to follow-up on the intervention effect. Statistical significance will be based on two-tailed tests, with p < 0.05 considered significant.

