### Baseline results

A total of 335 patients participated in this study: 185 in the ICDMS group and 145 in the control group. Only four patients in the control group declined to participate in the study.

Baseline clinical characteristics and demographic data for control and intervention patients are presented in Table 1. There were no significant differences between groups for known duration of diabetes, self-reported diabetes treatment, country of origin, smoking status, level of physical activity, Body Mass Index (BMI), weight and serum cholesterol. ICDMS patients were significantly younger, were less likely to be male, had significantly lower levels of education, higher levels of HbA1c, lower blood pressure, and were less likely to have neuropathy.

**Table 1 T1:** Demographic and clinical characteristics of participants in usual care (n = 145) and ICDMS (n = 185) groups.

	Usual Care		ICDMS		P
Age in years, mean (standard deviation (SD))	62.9	(11.6)	59.4	(13.4)	0.01

Duration of diagnosed diabetes in years, mean (SD)	13.7	(0.9)	12.8	(0.8)	0.47

Diabetes treatment					0.68

*Non-pharmacological*	5	(4%)	5	(3%)	

*Oral hyperglycaemics*	61	(46%)	68	(41%)	

*Oral hyperglycaemics and insulin*	41	(31%)	62	(37%)	

*Insulin only*	25	(19%)	32	(19%)	

Sex (male)	93	(64%)	83	(45%)	0.001

Country of origin					0.30

*Australia*	87	(61%)	78	(51%)	

*UK and Ireland*	13	(9%)	17	(11%)	

*New Zealand*	9	(6%)	7	(5%)	

*Europe*	12	(8%)	12	(8%)	

*Asia*	9	(6%)	13	(9%)	

*Other*	13	(9%)	26	(17%)	

Aboriginal or Torres Strait Islander	3	(2%)	8	(4%)	0.36

Smoking					0.74

*Never*	55	(42%)	64	(39%)	

*Ex-smoker*	59	(45%)	74	(45%)	

*Current smoker*	17	(13%)	26	(16%)	

Education level					0.51

*No formal qualifications*	36	(27%)	36	(23%)	

*School/Intermediate Certificate*	25	(19%)	34	(21%)	

*Higher School Certificate*	25	(19%)	40	(25%)	

*Diploma or Apprenticeship*	35	(27%)	42	(26%)	

*University Degree*	11	(8%)	8	(5%)	

BMI (kg/m^2^), mean (SD)	31.8	(6.3)	33.3	(8.3)	0.08

Weight (kg), mean (SD)	91.5	(22.5)	91.0	(25.9)	0.85

HbA1_c _(%), mean (SD)	7.9	(1.9)	8.5	(1.9)	0.001

HbA1_c _≤ 7%	54	(38%)	37	(22%)	0.003

Sitting systolic BP (mmHg), mean (SD)	140	(19)	130	(16)	<0.001

Sitting diastolic BP (mmHg), mean (SD)	77	(11)	72	(11)	<0.001

Blood Pressure ≤ 130/80 mmHg, mean	48	(33%)	99	(56%)	<0.001

Total Cholesterol (mmol/L), mean (SD)	4.2	(1.1)	4.3	(1.1)	0.47

HDL-cholesterol (mmol/L), mean (SD)	1.1	(0.3)	1.1	(0.4)	0.69

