The ICDMS is also not a general practice diabetes clinic where a general practice will have a clinical session devoted to the care of its patients with T2DM. Patients attending the ICDMS have been referred by their GP for specialist level care which is provided by the ICDMS multidisciplinary team. Once glycaemic control is achieved and the acute complications have been addressed, the patient is discharged back to their referring GP. The ICDMS does not provide a general practice service, and other health issues not related to diabetes are not addressed during the consultations, and patients are advised to discuss these issues with their own GP.

This study does have limitations. We have used a geographical control to assess the effectiveness of the ICDMS clinical model, as this was the most feasible study design in the health service environment in which the ICDMS was established. The differences at baseline between the intervention and control groups demonstrate the difficulties associated with this design, and the need to account for these differences in the statistical analysis. This research was conducted contemporaneously with the delivery of the clinical service. The majority of clinicians involved in the service were not researchers and were principally focused on clinical care rather than ensuring the integrity of the experimental design. At times this was challenging for the clinicians as they struggled with the relative rigidity of implementing a research protocol compared with clinical service delivery that can be adjusted as deemed appropriate by individual clinicians. Replication of this model of care requires a greater understanding of the impact of this model on the providers of care: their roles, satisfaction, and self-efficacy to provide treatment could be investigated through focus groups in both settings. However, this study focused on the impact of the model of care on clinical outcomes, rather than providers. Further research is needed to investigate the later important area.

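### In a non-randomised comparison, mandatory covariate adjustment is decided by baseline significance tests, so plausible predictors of HbA1c such as BMI, diabetes duration and treatment class need not be adjusted for

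*Protocol article*

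**What the plan says.** The Discussion states the design plainly: "We have used a geographical control to assess the effectiveness of the ICDMS clinical model". It also concedes "the need to account for these differences in the statistical analysis".

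The Statistical analysis section sets out the adjustment in three parts:

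- A mandatory screen: "Baseline characteristics that differ significantly between the two patient groups and the two groups of general practices will be identified". Whatever this screen picks out then enters every multivariate model. The only definition of significance given is "Statistical significance will be based on two-tailed tests, with p < 0.05 considered significant".
- One covariate fixed in advance: "Measures of the outcome value at baseline will be included in the regression analysis as a covariable". For the primary outcome this is baseline HbA1c.
- An optional remainder: "Other covariables may include any characteristics that are not balanced between the groups at baseline". No list is given and balance is not defined.

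The Baseline results section then reports how the screen falls out: "There were no significant differences between groups for known duration of diabetes, self-reported diabetes treatment", and likewise for country of origin, smoking, physical activity, BMI, weight and cholesterol. Age, sex, education, HbA1c, blood pressure and neuropathy are described as significantly different.

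**The concern.** Whether a covariate confounds the comparison depends on two things: how far the groups differ on it, and how strongly it predicts 12-month HbA1c. A baseline test addresses only the first, and does so imperfectly, because its p-value also moves with the number of patients, the amount of missing data and the number of categories. It carries no information on the second.

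In a randomised trial a poor covariate rule mainly costs precision. Here regression adjustment is the only control of confounding that the article describes, so a covariate left out can shift the estimate itself. The optional sentence does not repair this: it allows BMI to enter the primary model but does not require it, and gives no criterion for deciding. That part of the model therefore remains open when the outcomes are analysed.

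**Working it through.** **1. The plan's own scale.** The sample size section uses a 0.5% difference, SD 1.4%, two-sided 0.05 and 80% power. Per group, n = 2 × [1.4 × (1.960 + 0.842) / 0.5]² = 123; at the stated 120 the power is 79.0%, and 240 / 0.8 = 300. The figures reproduce to rounding. They do not bear on the covariate rule, but they supply the 0.5% used as the yardstick below.

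**2. What the screen can flag.** The standardised difference needed for p < 0.05 is 1.96 × √(1/n₁ + 1/n₂).

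- All patients, 145 v 185: 1.96 × 0.1109 = 0.217.
- Duration, 134 v 144 after missing data: 0.24.
- Retinopathy, 131 v 109: 0.25.

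More missing data therefore make adjustment less likely.

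**3. Applying the rule to Table 1.** For means, the standardised difference is the difference divided by √[(SD₁² + SD₂²)/2]. For categories, the multi-category version was computed from the printed counts.

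| Characteristic | Standardised difference (absolute) | p in Table 1 (recomputed) | Required by the rule? |
|---|---|---|---|
| Systolic BP | 10 / 17.56 = 0.57 | <0.001 (<0.001) | yes |
| Neuropathy | 0.53 | <0.001 (<0.001) | yes |
| Age | 3.5 / 12.53 = 0.28 | 0.01 (0.01) | yes |
| Country of origin | 0.29 | 0.30 (0.31) | no |
| Education | 0.21 | 0.51 (0.51) | text yes, table no |
| BMI | 1.5 / 7.37 = 0.20 | 0.08 (0.07) | no |
| Treatment class | 0.14 | 0.68 (0.70) | no |
| Duration | 0.09 | 0.47 (0.45) | no |

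- Country of origin has about the same standardised difference as age but fails the screen, because its test has 5 degrees of freedom. The two measures are not strictly comparable, but the contrast shows that the p-value does not track the size of an imbalance.
- For education, the Baseline results text reports a significant difference while Table 1 gives p = 0.51, which its counts confirm. The rule cannot be applied to education until the two are reconciled.
- The duration row treats the printed SDs (0.9 and 0.8) as standard errors, so the SDs are 0.9 × √134 = 10.4 and 0.8 × √144 = 9.6. Only that reading agrees with the stated p = 0.47.

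**4. Possible size of the bias.** For one omitted covariate, bias ≈ standardised difference × partial correlation r with 12-month HbA1c × SD. The documents give no r; 0.05 to 0.30 is assumed. The SD is 1.4 (planned) to 1.9 (Table 1 baseline).

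- Low end: 0.20 × 0.05 × 1.4 = 0.014, or 3% of 0.5.
- High end: 0.20 × 0.30 × 1.9 = 0.114, or 23% of 0.5.

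At the high-end assumptions, duration would give 0.09 × 0.30 × 1.9 = 0.05 and treatment class 0.14 × 0.30 × 1.9 = 0.08. Several omitted covariates could add up or cancel.

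**The case against.** The strongest reply is that baseline HbA1c, probably the best single predictor, is in the model whatever its p-value. This stands, and it pulls the plausible bias towards the lower end. If baseline and 12-month HbA1c correlate at 0.6 (an assumption), the residual SD is 1.9 × √(1 − 0.36) = 1.52, and BMI with a partial r of 0.1 gives 0.20 × 0.1 × 1.52 = 0.03. Adjusting for age, sex, blood pressure and neuropathy, which the rule does require, may absorb more.

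It is also fair that only BMI is a near miss. Duration (p = 0.47) and treatment class (p = 0.68) differ little between the groups. They belong in the model because they may be prognostic, not because they are badly imbalanced.

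Four stronger readings might be inferred, and the documents do not support them:

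- That the two adjustment sentences contradict each other. They can be read together: significant characteristics must be included, others may be. The fault is the undefined option. The mandatory set depends only on baseline data already tabulated, so it is not open to choice after outcomes are seen.
- That overlapping forms of one variable (HbA1c and HbA1c ≤ 7%, or three blood pressure terms) would enter one model. The rule speaks of characteristics and does not say this.
- That blood pressure was measured differently in the two groups. The description of the ICDMS assessment does not list blood pressure, and the Outcome assessment section describes medical record review without separating the groups. Foot screening is listed, but different ascertainment of neuropathy remains an inference.
- That the rule is merely detail left to an analysis plan. The article states the rule, so an unseen plan does not excuse it.

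**Conclusion.** The point holds as a flaw in a stated method. Significance at baseline is the wrong criterion for choosing confounders in a non-randomised comparison, and the article's own Table 1 shows it failing to require BMI, diabetes duration and treatment class and giving no clear answer for education.

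A reader might go further and conclude that the primary effect is confounded, or that the bias amounts to a quarter of the target or more. That is not shown. Nothing in the article links the omitted variables to 12-month HbA1c, so neither the size nor the direction of any bias can be derived. The range of about 0.01 to 0.11 HbA1c points per omitted covariate at 0.20 SD rests on the assumed partial correlation and on the choice of SD. The conclusion is that the rule may leave avoidable residual confounding and leaves part of the primary model to discretion.

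**What to change.** Replace the significance screen with one covariate list, chosen on prognostic grounds from data already collected and kept whatever the baseline p-values: baseline HbA1c, age, sex, BMI, diabetes duration, treatment class, education and smoking, plus systolic blood pressure and neuropathy. The last two are the largest imbalances in the table above and are adjusted for under the current rule, so a new list must not lose them. Use one form of each variable. If the team judges country of origin prognostic, it should be settled in the same list. Lock the list before 12-month outcomes are analysed, delete the sentence that makes further covariates optional, and report standardised differences in place of reliance on baseline p-values.

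Specify multiple imputation for missing baseline covariates. From the notes to Table 1, duration is missing in 11 + 41 = 52 of 330 patients (16%), 41 of them in the ICDMS group; education is missing in 13 + 25 = 38 and treatment class in 13 + 18 = 31. A complete-case model would lose at least 16% of patients, unevenly between the groups.

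The cost is modest. With Table 1 categories the list uses 7 single terms (HbA1c, age, sex, BMI, duration, systolic BP, neuropathy) + 3 (treatment) + 4 (education) + 2 (smoking) = 16 coefficients against about 330 patients, plus some imputation work. Sample size, alpha and trial conduct do not change.

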### Review and discharge

Phase Three focuses on execution of the management plan developed at the clinic, with the aim of discharging the patient back to their referring GP as soon as targets have been reached and stabilised. Patients newly commenced on insulin, or those who need their insulin regimens revised to achieve optimal glycaemic control are enrolled into the ICDMS insulin stabilisation service (ISS). Patients on the ISS are contacted two or three times a week by a diabetes nurse educator to review their daily blood sugar levels (BSLs). Under supervision of a GP Clinical Fellow, the diabetes nurse educator makes small, incremental adjustments to the patient's insulin regimen to achieve stable and optimal BSLs. Patients are reviewed at the weekly clinic as required to monitor and adjust other treatments. Where appropriate, patients are strongly encouraged to attend either the self-management or weight loss programs provided by the ICDMS or other relevant programs provided by the Inala Community Health Centre.

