## Methods/Design

### Study aim and design

The overarching aim of the ICDMS clinical model is to provide comprehensive and integrated clinical care for people with complex T2DM to achieve optimal glycaemic control. An open controlled intervention trial is comparing the impact of the ICDMS clinical model on patient outcomes compared to usual care provided to comparable patients attending the Princess Alexandra Hospital (PAH) Specialist Diabetes Outpatient Clinic. Figure 2 shows the study design. Usual care at the PAH involves assessment and review by a consultant endocrinologist or supervised training registrars or residents and referral to a diabetes nurse educator or other allied health personnel as required. Patients that have relatively stable control tend to not be discharged back to their referring GP, but continue to attend the clinic for annual reviews.

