### Sample size and power calculation

A total of 240 patients (120 per group) were needed to detect a difference between study groups of 0.5% in the change in HbA1c from baseline, assuming a standard deviation of HbA1c (our primary outcome) of 1.4%, using a 2-sided test with a significance level of 0.05 and 80% power. We estimated a 20% discontinuation rate for the 12 month follow-up period, thus we aimed to enrol 300 patients (150 per group).

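### Return-to-baseline imputation in the primary analysis dilutes a true 0.5% HbA1c difference to about 0.40% at the planned 20% loss, and is not reliably conservative if loss differs by arm

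*Protocol article*

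**What the plan says.** The Protocol article names the endpoint under Outcome assessment: "the primary outcome is HbA1c at 12 months". Under Statistical analysis, the primary analysis is on an "intention to treat basis assuming return to baseline values for any patients who do not complete follow-up", in a regression with the baseline value as a covariable. The same section plans a sensitivity analysis for loss to follow-up, with no method given, and a comparison of patients who complete with those who withdraw.

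Sample size and power calculation sets out to "detect a difference between study groups of 0.5% in the change in HbA1c from baseline". Its other inputs are an SD of 1.4%, a two-sided alpha of 0.05 and power of 80%. This gives 120 per group, raised to 150 per group for 20% discontinuation. The 20% is not split by arm.

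Three further statements bear on who may lack a 12-month value:
- Review and discharge describes ICDMS care "with the aim of discharging the patient back to their referring GP as soon as targets have been reached and stabilised".
- Study aim and design says that stable usual-care patients "tend to not be discharged back to their referring GP, but continue to attend the clinic for annual reviews".
- Outcome assessment takes baseline clinical data from medical records and adds: "Clinical data will be collected again at six and 12 months in similar fashions".

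**The concern.** Setting a missing 12-month HbA1c to baseline gives that patient a change of exactly zero. If patients who are lost respond as the others do, the between-group difference shrinks in proportion to the loss. The sample size does not allow for this: it treats the lost 20% as removed from the analysis with the effect intact, whereas the analysis keeps them with no effect.

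The rule also ignores the 6-month HbA1c, which the study plans to collect and which is informative about the 12-month value.

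The two services differ in how long they keep well-controlled patients. If that difference carries over into who has a 12-month HbA1c on record, the rule would assign no improvement to ICDMS patients who left because they had improved. The primary estimate would then partly reflect discharge practice rather than glycaemic effect.

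**Working it through.** **Inputs from the article.** Difference 0.5, SD 1.4, two-sided alpha 0.05, power 80%, 120 per group, 20% discontinuation, 150 per group after inflation. Table 1 gives baseline HbA1c means of 8.5 (ICDMS) and 7.9 (usual care), with SD 1.9 in each.

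**1. The plan's own figure.** n per arm = 2 × [1.4 × (1.960 + 0.842)/0.5]² = 123.1. Power at 120 per arm is Φ(0.5/(1.4 × √(2/120)) − 1.96) = Φ(0.806) = 79.0%. So 120 is a slightly rounded-down figure, and 240/0.8 = 300 is exact. The plan reproduces.

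**2. Dilution at the planned loss.** Let d be the loss and c the mean change in each arm, with loss unrelated to outcome. The expected difference is (1 − d_ICDMS) × c_ICDMS − (1 − d_UC) × c_UC. With d = 0.2 in both arms this is 0.8 × (c_ICDMS − c_UC) = 0.8 × (−0.50) = −0.40, whatever the usual-care change.

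**3. Power for 0.40 at 150 per arm.**
- SD 1.4: Φ(0.4/(1.4 × √(2/150)) − 1.96) = Φ(0.514) = 69.7%.
- The imputed zeros also reduce the variance. With no usual-care change, usual care has 0.8 × 1.96 = 1.568 and ICDMS has 0.8 × (1.96 + 0.25) − 0.40² = 1.608. The average is 1.588, so the SD is 1.26 and power is 78.5%.

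**4. Unequal loss (assumed rates, true difference −0.50).** The formula in step 2 gives:

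| Loss ICDMS / usual care | Usual-care change 0 | −0.3 | −0.5 |
|---|---|---|---|
| 20% / 20% | −0.40 | −0.40 | −0.40 |
| 30% / 10% | −0.35 | −0.29 | −0.25 |
| 10% / 30% | −0.45 | −0.51 | −0.55 |

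With no true effect and a common change of −0.5, 30%/10% loss gives 0.7 × (−0.5) − 0.9 × (−0.5) = +0.10, a false difference against ICDMS.

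**5. Loss linked to reaching target (assumed).** This was simulated as a baseline-adjusted regression with 400,000 patients per arm, the Table 1 baseline values and a true effect of −0.50.
- Milder mechanism: 40% missing among ICDMS patients at or below 7%, 10% among the rest (about 20% of the arm overall) and 10% in usual care, with change SD 1.4. The estimate is −0.30 if usual care does not change and −0.25 if it changes by −0.3. With no true effect and a common change of −0.3, it is +0.12 against ICDMS.
- Stronger mechanism: 20% ICDMS loss, all at or below 7.5%, with assumed slope on baseline 0.5 and residual SD 1.4. The estimate is −0.27 to −0.29 with 20% random loss in usual care, and about −0.2 to −0.3 across usual-care loss of 0 to 20% and usual-care changes of 0 to −0.5.

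The baseline covariable does not remove this bias.

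**6. A gap in the rule.** The notes to Table 1 show baseline HbA1c missing for 16 of 185 ICDMS patients and 1 of 145 usual-care patients. For any of these who are also lost, there is no baseline value to return to.

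**The case against.** **Discharge is not stated to be loss.** A reader might infer that ICDMS successes will be the patients without a 12-month HbA1c. The article does not support that as a fact. The imputation applies to patients who do not complete study follow-up, whereas the discharge text concerns the clinical service. The data source is medical records, not only the clinic's own. The service already uses existing pathology results and corresponds with referring GPs. How discharged patients are traced is detail that an article may leave to the full protocol. This objection stands, so the arm-specific bias is conditional.

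**The direction is not fixed.** A reader might also infer that greater loss in usual care always favours ICDMS, or that greater loss in ICDMS always dilutes. Neither holds. With 10%/30% loss and no usual-care change the estimate is −0.45, still diluted. With 30%/10% loss and usual care worsening by 0.8 it is 0.7 × 0.3 − 0.9 × 0.8 = −0.51, not diluted.

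**The harm to power may be small.** Once the SD shrinkage is counted, 78.5% is close to the 79.0% for 120 completers per arm. Enrolment of 185 and 145 also exceeds 300 in total; for a difference of 0.40 it gives 73.1% (SD 1.4) or 81.6% (SD 1.26). In a baseline-adjusted model the shrinkage is modest, with residual SD falling from 1.40 to about 1.32–1.35. This stands: the main damage is to the estimate, not to power.

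**The rule is prespecified and conservative, and mitigation is planned.** It is conservative under equal, non-informative loss, but step 4 shows that this fails under other patterns. The sensitivity analysis and the completer comparison are useful, but neither changes the primary estimate.

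**The alternative has its own assumption.** A mixed model or multiple imputation relies on data being missing at random, which cannot be tested and would favour ICDMS if its true dropouts relapse. That is a reason to keep return to baseline as a sensitivity analysis.

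**Conclusion.** The concern holds in a conditional form. The firm part rests only on the article's own figures: at 20% loss, equal and unrelated to outcome, the stated rule turns a true 0.5% difference into about 0.40%, while the sample size assumes 0.5%. Power at 150 per arm is then about 70% to 78%, depending on whether the SD shrinks.

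With unequal loss, the assumed scenarios give estimates from −0.25 to −0.55 for a true −0.50, so the rule cannot be relied on to be conservative. The loss rates by arm and the usual-care changes in those scenarios are assumptions.

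A bias against ICDMS, to about −0.2 to −0.3 for a true −0.50, follows only if patients discharged at target lack a 12-month HbA1c. The discharge and annual-review statements make that plausible; the article does not state it.

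**What to change.** - Make the primary analysis a likelihood-based repeated-measures model, or multiple imputation, using baseline and 6-month HbA1c, arm and the planned covariables.
- Keep return to baseline as a sensitivity analysis, and say how it handles patients with no baseline HbA1c.
- State that discharge from the service is not non-completion, and that a 12-month HbA1c is sought for every patient in both arms from medical records, including those of the referring GP or pathology provider.
- Report 12-month HbA1c availability by arm and, for ICDMS, by discharge status.

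The cost is a change of wording, modest programming and record requests. The new primary analysis relies on a missing-at-random assumption, which the retained return-to-baseline analysis helps to probe.
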